## Background

Australian obesity rates are amongst the highest in the world. Almost one in three Australian adults are obese (31%), and a further third are overweight (36%) [1]. Out of the 34 OECD countries, Australia’s adult obesity rate ranks 5th highest, and has shown large increases over the past 10 years, in contrast to counties that are reporting modest growth (Canada and Spain) or even stabilisation (US and UK) [2]. Excess weight, and obesity in particular, is a major risk factor for numerous health conditions including cardiovascular disease, type 2 diabetes, some musculoskeletal conditions and some cancers [3–5]. In 2017, the total annual cost of obesity in Australia was estimated at $11.8 billion [6]. Fully understanding the mechanisms underpinning obesity is crucial if targeted and effective obesity programs are to be developed.

The determinants of obesity are complex. Ecological models recognise they include individual, social, and environmental factors. In particular, excess energy intake through unhealthy eating patterns, insufficient energy expenditure due to lack of physical activity and excess sedentary behaviour, and unhealthy sleep, have been highlighted as key modifiable individual risk factors [7, 8]. Such risk factors are socially and geographically patterned and tend to cluster within individuals and families. In particular, people with lower socioeconomic status are more likely to be overweight or obese, this gap is wider in women, and people in regional areas are more likely to be overweight or obese [9]. Family factors, such as meal-time patterns, parenting style and work patterns have also been show to influence childhood obesity [10]. While we recognise that these determinants have genetic, social and geographical origins, less attention has been paid to temporal patterning.

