In sum, the evidence suggests that temporal patterning in activity and diet across the year leads to cyclical spikes in weight gain, which accrue over time. However, research to date has been piecemeal, focussed on only diet, or activity patterns or weight gain, and not all three simultaneously. Additionally, Australian data are lacking; it is possible that international findings may not reflect Australian patterns, due to key differences in timing of festivities by season (e.g. Australian Christmas falls in summer) and climate (e.g. Australian winters are relatively mild and summers relatively harsh). Finally, most research on the effects of daily physical activity, sedentary behaviour and sleep has examined the activities in isolation and applied standard multivariate statistical techniques which assume that daily activities are independent. However, activity data are naturally co-dependent – they occur in a finite 24-h window, thus if one activity increases (e.g. moderate to vigorous physical activity), then another must decrease (e.g. sleep). Research employing frequent waves of data collection, taking into account the compositional nature of activity data, is required to understand temporal patterns of weight gain, activity and dietary intake in order to enable the design and implementation of interventions at the time they are needed most. For example, if most annual weight gain occurs at Christmas, and this coincides with unhealthy eating patterns, dietary interventions could be targeted in the lead up to Christmas. This aims of this study are therefore to:
Describe the annual rhythms in adults’ body weight, daily activities and eating patterns, and determine whether changes in body weight across the year are associated with changes in activity and diet compositions.Determine whether changes in children’s body mass, activity and diet compositions are related to those of their parents, andExamine whether parental factors (parenting style and home environment) are associated with changes in children’s body mass, activity and diet compositions.

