#### Family environment

A range of family environment measures will be completed at baseline. Parenting style will be measured using the parenting warmth and parenting consistency scales from the Longitudinal Study of Australian Children [58]. Participants will report how they encourage their child’s physical activity on a 4-item scale adapted from adapted from ISCOLE Neighborhood and Home Environment Questionnaire [59] and describe how meals take place on the “Structure of Family Meals” subscale of the Meals in Our Household Questionnaire [60]. Participants will also report whether a TV, computer or video game system (non-hand held; PlayStation, Xbox, etc.) are in their bedroom and their child’s bedroom (adapted from ISCOLE [59]).

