### Statistical analysis

Longitudinal compositional data analysis methods will be used to assess activity and diet compositions. To account for the inherent co-dependency of compositional parts (proportions of time or macronutrients), compositions will be expressed as sets of isometric log ratios (ilrs) before their inclusion in statistical models [63, 64]. Aim 1 will use data from all participants. Aims 2 and 3 will use data only from parents/guardian of children enrolled in Life on Holidays and matched data from children in Life on Holidays.

#### Aim 1

Annual rhythms will be described graphically using Loess curves. Associations between change in weight (dependent variable) and changes in activity and diet compositions (independent variables) will be examined using multilevel modelling to adjust for non-independence of data, allowing for nesting of repeated measures within individuals and individuals within families. Diet and activity will be examined simultaneously to identify unique effects on weight. Covariates will include age, sex, socioeconomic status, and total energy intake.

#### Aim 2

Associations between change in children’s (dependant variables) and parents’ (independent variables) weight, activity, and diet compositions will be examined using a series of multilevel models to adjust for non-independence of data. Covariates will include parental and child age, sex, socioeconomic status, and child total energy intake.

#### Aim 3

Factor analysis will be used to derive factors from the baseline family environment items. The association between change in children’s body mass index z-score, and activity and diet compositions (dependant variables) and family environment (independent variable) will be examined using a series of multilevel models. Covariates will include parental and child age, sex, socioeconomic status, and total energy intake.

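### Adjusting the Aim 2 and Aim 3 child body-mass models for total energy intake estimates an association net of intake, not the overall association that the aims ask about

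*Protocol article*

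**What the plan says.** The Statistical analysis section gives each aim a single covariate list. For Aim 2, which relates change in children's weight, activity and diet compositions to the same quantities in parents, it is: "Covariates will include parental and child age, sex, socioeconomic status, and child total energy intake". For Aim 3, which relates family-environment factors to change in child BMI z-score, activity and diet compositions, it is: "Covariates will include parental and child age, sex, socioeconomic status, and total energy intake". Both aims are to be met by a series of multilevel models. Neither list is divided by outcome, and no model without energy intake is described.

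The aims stand at the end of the Background subsection on weight gain across the year. Aim 2 is to "Determine whether changes in children’s body mass, activity and diet compositions are related to those of their parents". Aim 3 asks, in similar terms, about parenting style and the home environment. Neither asks for a relation that is independent of how much the child eats.

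Earlier in the Background, "excess energy intake through unhealthy eating patterns" is among the key modifiable individual risk factors for obesity. The same section states: "Family factors, such as meal-time patterns, parenting style and work patterns have also been show to influence childhood obesity". Under Measures, Family environment, participants also "describe how meals take place on the “Structure of Family Meals” subscale of the Meals in Our Household Questionnaire", and Aim 3 derives its factors from the items in that subsection.

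**The concern.** A covariate that lies between exposure and outcome takes out of the exposure coefficient whatever passes through it. If family meals or parental diet affect a child's body mass partly through how much the child eats, a model that holds the child's intake fixed reports only the remainder. That remainder can be worth knowing, but it answers a different question from the one in the aims.

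The Discussion would use parent-child concordance to support well-timed family-based interventions. Such interventions may act through children's intake, so the body-mass models would set aside one of the channels of most interest.

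**Working it through.** **1. Is there a plan figure to reproduce?** No. The power calculation concerns Aim 1 only. The article gives no effect size, sample size or mediation share for Aims 2 and 3.

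**2. Does intake lie on the path, by the article's own account?** Set side by side:
- Intake to body mass: the Background names excess energy intake as a key modifiable risk factor.
- Family factors to child body mass: the Background names meal-time patterns and parenting style.
- Family meals among the exposures: the meal-structure subscale is one of the Aim 3 family-environment measures.

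The link from family factor to child intake is not stated, but it is the natural reading for meal structure and for parental diet.

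**3. Is there a compositional reason for the covariate?** Log-ratio coordinates carry shares and no absolute amount, so total energy is a natural complement where diet composition is an exposure or the outcome.
- Aim 1 has the participant's own diet composition as exposure, so adjustment for total energy is coherent there. Aim 1 also says that it seeks the separate contributions of diet and activity; Aims 2 and 3 carry no such wording.
- In Aim 3 the exposure is family environment.
- In Aim 2 the diet exposure is the parent's, so the complementary total would be the parent's, yet the covariate is the child's.

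For child body mass, this logic gives no reason to include the child's intake.

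**4. What does adjustment do? (All effect sizes are assumed.)** Let the exposure X and intake M have unit variance, with M = aX + error and body mass Y = dX + bM + error. Then:
- coefficient of X without intake = d + ab (the total);
- coefficient of X with error-free intake = d;
- with measured intake of reliability 0.5 (error variance 1), the coefficient on measured intake is b(1 − a²)/(2 − a²), so the coefficient of X is d + ab/(2 − a²).

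Take a total of 0.20 SD and b = 0.4. If a share m is mediated, a = 0.20m/0.4 and d = 0.20(1 − m).

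| m | a | d | ab | Without intake | Adjusted, no error | Adjusted, reliability 0.5 |
|---|---|---|---|---|---|---|
| 0% | 0 | 0.20 | 0 | 0.20 | 0.20 | 0.200 |
| 25% | 0.125 | 0.15 | 0.05 | 0.20 | 0.15 | 0.175 |
| 50% | 0.25 | 0.10 | 0.10 | 0.20 | 0.10 | 0.152 |
| 75% | 0.375 | 0.05 | 0.15 | 0.20 | 0.05 | 0.131 |
| 100% | 0.5 | 0 | 0.20 | 0.20 | 0.00 | 0.114 |

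A simulation of 1,000,000 records per row agrees: 0.147, 0.102, 0.050 and −0.001 for the error-free column from 25% down, and 0.172, 0.154, 0.131 and 0.113 for the last column. With error, the adjusted coefficient is neither the total nor the direct association.

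**5. Activity outcomes.** Nothing in the article puts intake between parent or home and child activity. If intake instead follows activity with coefficient g, and X has a 0.20 effect on activity, the adjusted coefficient is 0.20 × [1 − 0.96g²/(1 − 0.04g²)].
- g = 0: 0.20.
- g = 0.2: 0.20 × (1 − 0.0384/0.9984) = 0.192.
- g = 0.4: 0.20 × (1 − 0.1536/0.9936) = 0.169.

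This is mild attenuation from conditioning on a consequence of the outcome. It is not mediation.

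**The case against.** **The article is condensed.** A short summary list may be refined by outcome in an analysis plan, and intake is proper for one of the three outcome types. That is possible. But the article does not leave the choice open: it names the covariate for each whole series and describes no alternative. Followed as written, the body-mass models include it.

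**The aims speak of relation and association.** They do not speak of total or causal effects, and the Background lists intake and family factors as separate determinants without saying that one acts through the other. This stands. The point is a mismatch between the question and the adjusted coefficient, and the mediator is plausible rather than established.

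**Aim 3 does not say whose intake is meant.** Aim 2 says the child's. If Aim 3 means the parent's, the mediator argument is weaker there. This stands and is itself something to settle.

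**Many exposures have other routes.** Encouragement of physical activity, screens in bedrooms, and parenting warmth and consistency can reach body mass without passing through intake, and factor analysis pools them with meal structure. A reader might infer that adjustment removes the whole effect sought. The article does not support that: only the share carried by intake goes, and total removal needs full mediation and error-free intake.

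**Direction is not guaranteed.** Shrinkage towards zero needs direct and indirect effects of the same sign, and no unmeasured cause of both intake and body mass. The article establishes neither.

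**Conclusion.** The concern holds for change in child weight (Aim 2) and child BMI z-score (Aim 3). As specified, those models estimate an association net of energy intake and do not answer the overall question in the aims. In Aim 3 this depends on the child's intake being the one meant.

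The size is unknown. The 0.20 SD effect, the mediation shares and the reliability of 0.5 are assumptions. At 50% mediation the adjusted model keeps 0.10/0.20 = 50% of the association if intake is error-free, and 0.152/0.20 = 76% at reliability 0.5. How child intake is measured belongs to the linked children's study, which is not shown.

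Three stronger readings are tempting and should not be drawn:
- That the activity models suffer the same mediation problem. No passage supports such a path; there, intake is at most an unneeded covariate or a consequence of activity.
- That the R² of 0.10 in the power calculation would fall by a stated amount. That figure is for adult weight in Aim 1 and does not carry over.
- That a real family effect would be reported as null. No effect size or precision is given for Aims 2 and 3, so this cannot be shown.

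**What to change.** - **Child body mass (weight in Aim 2, BMI z-score in Aim 3):** make the model without total energy intake primary. Report the energy-adjusted model as a secondary analysis, labelled as an association net of intake.
- **Child diet composition:** keep the energy adjustment.
- **Child activity composition:** drop energy intake or give the reason for it.
- **Aim 3:** state whether the intake is the child's or the parent's.
- **Aim 1:** no change.

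The cost is one line of covariate specification and one extra table. No new data are needed.

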## Discussion

A main strength of this study is its novelty — it will be the first in the world to simultaneously examine temporal patterns in weight, daily activities and diet. Additional strengths are the use of wireless tracker technology and wifi scales to provide high fidelity information about adults’ activity patterns and weight changes across the full year, with low participant burden. The study will use a compositional analysis approach, which is quickly gaining traction in time-use epidemiology. In addition, the opportunity to link parents’ and children’s data will allow examination of the interplay between temporal and family determinants of obesity.

Potential limitations must also be acknowledged. The study only targets adults who are parents. While the majority of Australian adults are parents (approximately 75% of 45–49 year old Australian women have children [65]), we acknowledge that their data may not represent adults who are not parents, or likewise those who are not motivated to participate in a research study. In addition, participants are recruited from a single Australian city (Adelaide, population 1.3 million); however, surrounding areas are included so that participants are drawn from metropolitan, suburban areas, and rural areas. It is possible that the weighing regimen may cause reactivity, given that frequent self-weighing can be an effective weight intervention strategy [66]. Reactivity will be reduced by allowing weekly weighing (i.e. not enforcing daily weighing), explaining to participants that the purpose of the study is to monitor usual lifestyle (not intervene), and through use of automated data collection (preventing the need for journaling).

With nearly one-third of Australian adults obese, a further one-third overweight, and rates continuing to rise, obesity is one of the greatest health challenges facing Australia. To date, public health obesity campaigns have typically intervened by geography (e.g. rural and remote), demography (e.g. targeted ethnic groups) or socioeconomically (e.g. low SES families). However, it appears likely that temporal factors, such as day type, cultural celebrations and season, may also play a key role in weight gain. It is hoped that this study’s findings will reveal critical moments for intervention to assist the prevention of weight gain.

Furthermore, the study will examine the interplay between temporal and family determinants of obesity. If our results reveal intergenerational concordance in temporal patterns of weight gain, activity and diet compositions, this would suggest that carefully-timed, family-based interventions could be an important intervention strategy. Recent research suggests that parent-child obesity interventions may be a particularly effective [67], yet under-used, intervention strategy.

## Data Availability

N/A

## Abbreviations

DASS-21: Depression Anxiety Stress Scale
DQES: Dietary Questionnaire for Epidemiological Studies
Ilrs: Isometric log ratios
WHOQOL-BREF: World Health Organization Quality of Life assessment 26-item version
